**Figure 1 F1:**
[figure not shown]
CONSORT schema.

#### Data collection

As this is a feasibility study, it is not formally testing hypotheses. Nevertheless, we will examine outcome measures pre/post/follow-up (baseline, end of intervention and six-month follow-up) to evaluate the indicative effect of the intervention on both individual and couple/relational issues. Outcome measures have been selected to prevent over-burdening participants (by capping the length and number of measures used). We have generously estimated that all measures may take 30 minutes to complete, but feel that many participants will complete them in 10 minutes. Validated measures, detailed below, will be used alongside a specially designed *pro forma* for collating additional information on health-service use and demographic data.

In order to assess the feasibility and acceptability of the intervention, practitioners will complete adherence checklists, indicating for each couple which components of the intervention were covered in the therapy.

#### Outcome measures

The primary outcome measure (see below) assesses sexual functioning as part of a broader health-related quality-of-life measure. The secondary measures reflect the evidence that men and their partners require psychological (anxiety, depression), relational and sexual components to an intervention to meet the needs of this group.

Primary outcome measure

● Sexual functioning - EPIC measures general and sex-specific items related to prostate cancer [46]. EPIC is a comprehensive instrument that evaluates patient function and ‘bother’ after prostate cancer treatment. Potency of ≤60 in the sexual function domain is a clinical cut-off [42].

Secondary outcome measures

● Anxiety and depression - Hospital Anxiety and Depression score (HADS) measures psychological impact [61].

● Functional couple relationship - systemic core outcome measure (SCORE 15) measures relationship changes [62].

● Use of health services and erectile dysfunction medication/technologies, collated via a self-report questionnaire designed by the investigators.

Outcome measures will be assessed at baseline, at end of intervention and six months later.

#### Statistical analysis

Although hypothesis testing should proceed cautiously in a feasibility/acceptability study, we anticipate that couples in the intervention group will show increased scores for sexual functioning (measured using EPIC) and functional couple relationship (SCORE 15 measure), and decreased scores for anxiety and depression (HADS measure).

The study will therefore estimate the efficacy of this intervention based on the mean difference in primary (EPIC) and secondary outcome measures (SCORE 15, HADS) between the intervention and control groups pre- and post-test. Baseline demographic characteristics will be reported as mean and standard deviation for continuous data and number (percentage) for categorical data. ANOVA will be used to test the within-between group interaction in this two-group design, with two points of measurement (end of intervention and six-month follow-up). Data will be managed and analysed using SPSS version 19 (IBM Corp, Armonk, NY, USA). The significance level applied to all analyses (and any adjustments for *post hoc* analyses) will be set at 0.05.

Analysis of the practitioner adherence checklist data will proceed using frequency counts to identify those areas addressed most frequently. This data will be interpreted with reference to the qualitative appraisal of feasibility and acceptability.

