#### Sample size calculation

The trial aims to recruit 68 men and partners at routine follow-up after surgery, with 30% over-recruitment to enable adjustment for loss to follow-up [43]. A sample size of 68 couples was calculated using G-Power [44] based on having 90% power to detect a small-to-medium effect size *f* of 0.20 on the primary outcome (using repeated measures analysis of variance (ANOVA) and testing the within-between group interaction in this two-group design with two points of measurement (end of intervention and six-month follow-up) at an alpha level of 0.05). A small-to-medium effect on sexual function was selected based on previous intervention effects seen for couple interventions in the cancer literature [45].

Assuming a baseline mean of 33 and a standard deviation of 24 on the sexual function subscale of the EPIC [46], this study will have 90% power to detect a mean difference of 9.6 units at the 0.05 level. This will allow the study to estimate the efficacy of this intervention on the mean difference in overall sexual function (as measured by EPIC) between the intervention and control groups pre- and post-test. The standardised difference observed will be used to calculate the sample size required for a definitive trial to test the efficacy of this intervention. The anticipated effect size of *f* of 0.20 on the primary outcome is a crude estimate, as it is based on a pooled estimate of a heterogeneous selection of couple interventions for several types of cancer [45].

Based on surgical data from the locale (2009 to 2011) we estimate that there will be 500 patients who will be between 12 weeks and two years from surgery during the one-year recruitment period. The estimated recruitment rate from a prior study with a similar population and intervention design was 21% [33]. As some of the patient population will be excluded from the study based on the eligibility criteria above, we anticipate contacting approximately 420 patients to recruit 88 couples (taking account of 30% over-recruitment [43] to achieve a sample size of 68 couples completing the study).

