### Phase 1: designing the intervention

The intervention will be informed by the extant literature regarding the pragmatics and focus for the couple work. It will consist of six sessions [34,35] conducted every two to three weeks [28,47] by registered practitioners at a local voluntary sector counselling organisation. The intervention will be delivered off-site in central Edinburgh, away from the pressures of a busy outpatient hospital clinic where there is usually limited time to discuss psychosexual concerns during healthcare consultations [24].

The content of the intervention will comprise assistance with emotional disclosure [33,48], psycho-education [19,29], relational and sexual needs [29-31] and dyadic adjustment and coping [49,50]. A treatment manual will be developed to guide delivery of the intervention [51]. The manual will comprise information about prostate cancer and its effects, principles of therapeutic change, guidance on using the manual and a detailed session structure plan. This manual-based family-relational-psychosexual support will be based on systemic principles [52-55] combined with techniques from sex therapy, that is, sensate focus [56]. Therefore, the manual aims to integrate components of systemic theory with elements of sex therapy to support intimacy and emotional aspects of the couple relationship.

Specialist training in delivery of the intervention will be provided to practitioners holding accredited counselling or psychotherapy qualifications. Training will include sessions led by men affected by prostate cancer and a systemic practitioner in cancer care. Fidelity to the manual will be assessed as an ongoing process, recorded by practitioner self-report using a checklist provided by the research team.

In line with routine counselling interventions, this study adopts a waiting-list control design [57]. The control group will be offered the intervention if the analysis indicates a significant benefit in quality of life for couples who receive the support.

The session structure for the intervention will cover six main topic areas as follows:

**Session 1 - Getting to know the couple: orientation and engagement.** This first session will outline the support on offer. Topics for discussion will include:

● the couple’s definition of current issues, concerns and problems

● the cancer diagnosis and treatment(s)

● the partner’s role in the context of diagnosis and treatment

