### Ethical considerations

The study has been approved by NHS West of Scotland Research Ethics Committee (Reference: 12/WS/0255). Management approval for recruiting at the Western General Hospital site has been obtained from NHS Lothian. A detailed information sheet will be provided to participants with study information and contact details. Informed consent will be obtained from all patients and partners who agree to participate in the study. Additional consent will be sought from those couples and healthcare professionals who agree to take part in post-intervention acceptability/feasibility interviews. If consent is given by participants, GPs will be advised of their patient’s involvement in the trial. Couples in the trial will consent to having their baseline summary scores communicated to the practitioners delivering the intervention; the use of outcome measures is routine practice and helps practitioners tailor their approach to couples.

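### Practitioners treat the intervention arm only, but neither the between-arm mean difference nor the stated basis for sizing the definitive trial allows for clustering by practitioner

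*Protocol article*

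**What the plan says.** The section on designing the intervention (Phase 1) has the six sessions delivered "by registered practitioners at a local voluntary sector counselling organisation". Under Randomisation, allocation concealment and blinding, controls receive their usual hospital follow-up. Phase 1 adds that they are offered the therapy later only if the analysis shows a benefit. During the trial, therefore, practitioners are attached to one arm only.

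The Statistical analysis section names the difference in mean outcome between arms, pre- to post-test, as the efficacy estimate. For the test it says "ANOVA will be used to test the within-between group interaction in this two-group design", using the end-of-intervention and six-month measurements. Practitioners enter that section only through the adherence checklists, which are summarised as frequency counts of the areas addressed. The Data collection section has practitioners complete a checklist for each couple.

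On the next trial, the Sample size calculation section says: "The standardised difference observed will be used to calculate the sample size required for a definitive trial to test the efficacy of this intervention". Objective 3 makes that sample size a product of the pilot. No section mentions a practitioner effect, an ICC or a design effect, and none gives the number of practitioners or the couples each will see.

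**The concern.** When one practitioner treats several couples, those couples' outcomes may be more alike than outcomes of couples treated by different practitioners. The intervention mean then rests on fewer independent pieces of information than the number of couples suggests. The control mean does not have this problem. An analysis that treats all couples as independent gives too small a standard error for the difference between arms.

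The larger stake is the definitive trial. Even if the pilot's effect estimate were exactly right, a calculation based on the standardised difference with no allowance for practitioners would ask for too few couples wherever practitioners differ. The pilot is also the natural place to see whether results vary visibly between practitioners, but no stated analysis looks.

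Some variation in delivery is plausible despite the manual: sex-therapy techniques are applied where they suit the couple, Session 5 is set by practitioner and couple, and fidelity is recorded by practitioner self-report.

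**Working it through.** **Inputs from the protocol.** 68 couples completing, allocated 1:1, so 34 per arm; effect size f = 0.20; 90% power; alpha 0.05; two groups; two measurements (Sample size calculation; Randomisation, allocation concealment and blinding).

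**Inputs not in the protocol, so assumed.** Number of practitioners k = 2, 4 or 6 with equal caseloads; ICC = 0.02, 0.05 or 0.10; correlation between the two measurements rho = 0.5.

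**The plan's own figure.** "A sample size of 68 couples was calculated using G-Power". For the within-between interaction, the noncentrality is f² x N x (measurements) / (1 - rho) = 0.04 x 68 x 2 / 0.5 = 10.88, on 1 and 66 degrees of freedom. Power is 0.9015, and 68 is the smallest even total that reaches 90%. With rho of 0, 0.3 or 0.7 the total would be 134, 94 or 42. The stated 68 is thus reproduced exactly with every couple independent, and contains no allowance for practitioners.

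**Variance of the between-arm mean difference.** Let n = 34 per arm, m = 34/k couples per practitioner, and s² the outcome variance.
- Intervention mean: s²/n x DE, with DE = 1 + (m - 1) x ICC.
- Control mean: s²/n.
- Variance relative to independence: R = (DE + 1)/2 = 1 + (m - 1) x ICC / 2.

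| Practitioners | m | R at ICC 0.02 | R at ICC 0.05 | R at ICC 0.10 |
|---|---|---|---|---|
| 2 | 17 | 1.16 | 1.40 | 1.80 |
| 4 | 8.5 | 1.08 | 1.19 | 1.38 |
| 6 | 5.7 | 1.05 | 1.12 | 1.23 |

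Worked case, 4 practitioners, ICC 0.05: DE = 1 + 7.5 x 0.05 = 1.375 and R = 2.375/2 = 1.19. The true standard error is sqrt(1.19) = 1.09 times the unadjusted one. A nominal 5% test of the mean difference has actual error 2 x (1 - Phi(1.96/sqrt(1.19))) = 7.2%. With 2 practitioners: DE = 1 + 16 x 0.05 = 1.80, R = 1.40, error 9.8%.

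**Definitive trial at the same caseload m.** Multiply the intervention arm by DE and leave the control arm at n. The variance becomes s² x DE/(n x DE) + s²/n = 2s²/n, which is the precision intended under independence. The total goes from 2n to n(1 + DE), a ratio of (1 + DE)/2 = R. The percentages in the table therefore apply to its size too.

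**The interaction test.** Write the outcome of couple i with practitioner j at time t as mean(t) + u(j) + e(i,j,t). The change from end of intervention to six months contains no u(j), so a constant practitioner effect cancels. Only an effect that grows or fades between those times counts. From baseline to a later time it does not cancel, because no therapy has been given at baseline.

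**The case against.** The strongest reply is that this is detail for an analysis plan: a journal article describes the model in one sentence and excludes nothing. That is fair for a practitioner-effect sensitivity analysis. It is less persuasive for the definitive trial's size, whose basis the article itself states and which is one of its objectives.

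Second, this is a pilot. The Data collection section says it does not formally test hypotheses, so an error rate of 7% rather than 5% matters little here. That stands, although the Discussion expects to have determined whether the intervention is effective. The sizing point does not depend on any test in the pilot.

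Third, the facts are thin. A reader might infer that a handful of practitioners each carry a large caseload. That is plausible for specially trained staff of one organisation, but the protocol does not say it. Nor does it show that sexual function varies by practitioner. The remark that "the use of outcome measures is routine practice and helps practitioners tailor their approach to couples" concerns fitting the work to each couple and is not evidence that one practitioner's couples become alike. With 6 practitioners and ICC 0.02 the increase is about 5%, which is negligible in a pilot.

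Fourth, a reader might infer that the planned ANOVA interaction has a 7% to 10% error rate. The documents do not support that: the interaction is stated for the end-of-intervention and six-month points, where a constant practitioner effect drops out. Those rates belong to the between-arm mean difference.

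Fifth, a reader might infer that the definitive trial will certainly be undersized. The protocol says that the observed standardised difference will be used, not that it will be the only input. An ICC allowance can still be added later, provided the practitioner of each couple is kept. The per-couple checklist probably allows this already, but no stated analysis uses the link.

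**Conclusion.** The point holds in a limited form. Couples are nested within practitioners in the intervention arm only. The efficacy estimate and the stated basis for sizing the definitive trial make no allowance for this. Under the assumed range, the variance of the between-arm mean difference is understated, and a definitive trial at the same caseload would need enlarging, by about 5% to 80%, with 19% as a middle case (4 practitioners, ICC 0.05). The range rests wholly on assumed practitioner numbers, equal caseloads and assumed ICCs. If practitioners do not differ, nothing is lost. The consequence is mainly for the definitive trial and is modest for the pilot's own conclusions. The change is cheap and worth making.

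**What to change.** 1. Put a practitioner study number on the existing per-couple adherence checklist and link it to the couple's outcome record.
2. State the number of practitioners and the couples each treated, and report EPIC change and checklist adherence by practitioner, descriptively.
3. Fit a practitioner effect in the intervention arm only as a sensitivity analysis for the between-arm mean difference, and only if there are enough practitioners. With 2 to 4, a random effect is barely estimable and cluster-robust standard errors are unreliable even with a small-sample correction.
4. In the definitive-trial calculation, multiply the intervention arm by 1 + (m - 1) x ICC, with m the caseload planned for that trial, over a stated assumed range such as 0.02 to 0.10. Do not rely on the pilot's own ICC, which will be imprecise.

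The cost is one identifier on an existing form, a little more analysis, and a somewhat larger definitive sample size.

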## Abbreviations

ANOVA: repeated measures analysis of variance; EPIC: Expanded Prostate Cancer Index Composite; GP: general practitioner; GS: Gleason score; HADS: Hospital Anxiety and Depression score; MRC: Medical Research Council (United Kingdom); NHS: National Health Service (United Kingdom); PSA: prostate-specific antigen; RCT: randomised controlled trial; SCORE 15: systemic core outcome measure; TNM: tumour, node and metastases; UK: United Kingdom.

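### The named repeated-measures ANOVA uses only men with both follow-up scores; a mixed model would keep partial data and guard against bias if loss is arm-related

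*Protocol article*

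**What the plan says.** Under Statistical analysis, the protocol article states that "ANOVA will be used to test the within-between group interaction in this two-group design", "with two points of measurement (end of intervention and six-month follow-up"). The Abbreviations list fixes the meaning of the term: "ANOVA: repeated measures analysis of variance". The software is named too: "Data will be managed and analysed using SPSS version 19". The same section describes the efficacy estimate separately, as a mean difference in EPIC, SCORE 15 and HADS "between the intervention and control groups pre- and post-test".

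The Sample size calculation rests on the same ANOVA, with "90% power to detect a small-to-medium effect size" f of 0.20, "at an alpha level of 0.05". It plans 88 recruited couples "to achieve a sample size of 68 couples completing the study", and it says that the standardised difference observed will be used to size a definitive trial. Over-recruitment is the only provision for loss to follow-up that the article describes. The section on randomisation places allocation after consent and return of baseline data, which implies that about 88 couples are randomised; the abstract says 68.

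**The concern.** A classical repeated-measures ANOVA needs a complete row for each man. With two post-baseline time points, a man who returns the end-of-intervention form but not the six-month form contributes nothing, and neither does a man with the reverse pattern. Over-recruitment restores the number of complete rows. It does not restore the comparability of the arms if the men who leave differ between arms.

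Arm-related loss is plausible here. Blinding is not possible, only one arm is asked to attend six off-site sessions, and the plan logs attrition at each stage of the intervention. The arm difference from this pilot is meant to feed the sample size of the definitive trial, so an overestimate would make that trial too small.

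**Working it through.** **Inputs from the protocol article.** f = 0.20, power 90%, alpha 0.05, two groups, two time points, 68 completing, 88 recruited, 30% over-recruitment, about 420 contacted at a 21% recruitment rate, SD 24, detectable difference 9.6.

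**Inputs not given, so assumed.** The correlation between repeated measures, and the timing and mechanism of loss.

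**1. The plan's own figures.** For the within-between interaction with m = 2 time points, the noncentrality is λ = f²·N·m/(1 − ρ), with 1 and N − 2 degrees of freedom.
- With ρ = 0.5 and N = 68, λ = 0.04 × 68 × 2/0.5 = 10.88 and power is 0.9015, so 68 is reproduced. It depends on the unstated correlation: N = 94 at ρ = 0.3 and N = 42 at ρ = 0.7.
- 68 × 1.3 = 88.4, and 420 × 0.21 = 88.2; both give 88.
- Planned allowance for loss: 88 − 68 = 20 couples, and 20/88 = 22.7%.

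**2. Precision at end of intervention.** Let q be the share lost and a the part of that loss that occurs before the first post-test. If loss is random, the standard error of a completers-only analysis, relative to one that uses every end-of-intervention score, is about √[(1 − aq)/(1 − q)]. With q = 0.21:
- all loss after the first post-test (a = 0): √(1/0.79) = 1.125;
- half before it (a = 0.5): √(0.895/0.79) = 1.064;
- all before it (a = 1): 1.00.

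A simulation with a = 0 gave standard errors of 3.87 and 3.46, a ratio of 1.12. The range is therefore 0% to about 12%. If exactly 20 of 88 were lost, all after the first post-test, the same arithmetic gives √(88/68) = 1.14.

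**3. Bias, first set of assumptions.** 44 per arm, SD 20, correlation 0.6, true effect 6 points at both times, about 21% lost after the first post-test, 4,000 trials per scenario, baseline-adjusted arm differences.
- Intervention-arm loss related to poor early change (log-odds 1 per SD): completers-only estimates 8.7 at end of intervention (+44%) and 6.9 at six months (+16%; percentages from unrounded means). An independent run gave 8.6 and 7.0. Likelihood-based estimates from all available data: 6.0 and 5.9.
- Same mechanism with a true effect of zero: completers-only 2.5 and 0.9; all-data estimates about 0.
- Random loss: no bias.

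**4. Bias, second set, with the plan's SD of 24 and effect of 9.6.** Correlation 0.5, 22.7% missing at six months, differences in change from baseline among completers.
- Random loss: 9.7 and 9.7.
- Poor responders leave under the same rule in both arms: 8.4 and 9.1, a modest bias towards zero. With a true effect of zero there is no bias.
- Poor responders leave only the intervention arm: 14.2 and 11.9. The between-arm difference in change from end of intervention to six months, which is the contrast that the named interaction tests, is −2.3 when the truth is 0, an apparent fading of effect.
- An estimate that uses all observed data gives 9.6 to 9.7 at six months in all three cases.

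**5. Consequence for the definitive trial.** Required N varies as 1/effect². An overestimate of 44% gives 1/1.44² = 0.48 of the N needed; 16% gives 1/1.16² = 0.74.

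**The case against.** A reader might infer that the ANOVA throws away 20 of 88 randomised couples. The documents do not support that. The 20 is a planning allowance. Couples who return neither follow-up give no post-baseline score to any method, a mixed model included. Only men with exactly one follow-up are lost because of the ANOVA, and the article does not say how many are expected. That 88 are randomised is itself an inference, at odds with the abstract.

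A reader might also infer that the efficacy estimate will be too large. That needs loss of poor responders mainly in the intervention arm. The article gives no loss pattern, and other plausible patterns give no bias or a bias towards zero. The +44% and +16% rest on an assumed SD, correlation, effect and strength of loss. They also concern arm differences at each time, whereas the quoted ANOVA tests an interaction over two post-baseline points. The efficacy estimate is worded separately, and nothing states that it is confined to couples with both follow-ups.

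Further, analysis sets and imputation are commonly left to a statistical analysis plan, and sizing on completers is ordinary practice. The study puts feasibility and acceptability first and says that it does not formally test hypotheses. All of this stands, and it limits the weight of the point. It does not remove it: the article names a specific method, and that method on the observed data cannot use a man with one follow-up score.

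**Conclusion.** The point holds as a cheap improvement to the analysis, not as a demonstrated error in the result. The named ANOVA needlessly loses men with one follow-up, in a study that allows for 22.7% non-completion. The cost in precision at end of intervention is between 0% and about 12%, set by the unknown timing of loss. Upward bias in completers-only arm differences is a conditional risk, illustrated at +16% to +44% if poor responders leave mainly the intervention arm. It is absent under random loss, and slight or towards zero under a common loss rule. It deserves attention because the pilot's standardised difference is to be carried into the definitive sample size.

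**What to change.** Make the efficacy analysis a linear mixed model for repeated measures on all randomised couples as allocated. Use every available follow-up score, with baseline EPIC as covariate and arm, time and arm × time as effects. Report the arm difference with its 95% CI at end of intervention and at six months. Keep the ANOVA on men with both scores as a sensitivity analysis. Reconcile the abstract's 68 randomised with the 88 recruited and 68 completing in the Sample size calculation.

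The cost is a rewritten analysis paragraph, plus an aligned sample-size paragraph, since that calculation is built on the ANOVA interaction. No new data are needed: baseline scores are collected before randomisation, and the planned package fits the model. Two limits remain. The model assumes data missing at random, and couples with no follow-up still add no outcome information.

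### The named efficacy test uses only the two post-baseline visits, so it cannot detect a benefit that is equal at end of intervention and at six months

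*Protocol article*

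**What the plan says.** The Statistical analysis section of the protocol article names one test for the outcome measures, an ANOVA to "test the within-between group interaction in this two-group design, with two points of measurement (end of intervention and six-month follow-up". The Sample size calculation section sizes the trial on the same test with the same two occasions: "testing the within-between group interaction in this two-group design with two points of measurement (end of intervention and six-month follow-up". It reports 68 couples for 90% power at effect size f = 0.20 and alpha 0.05. Neither section names baseline as an occasion or as a covariate.

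Other statements point to a different comparison:

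- Statistical analysis bases the efficacy estimate on the mean difference in EPIC, SCORE 15 and HADS "between the intervention and control groups pre- and post-test". The Sample size calculation section describes the EPIC contrast in the same terms.
- Data collection says "we will examine outcome measures pre/post/follow-up (baseline, end of intervention and six-month follow-up", which is three occasions. Outcome measures gives the same schedule.
- Randomisation, allocation concealment and blinding says baseline outcome data are returned before allocation, so baseline EPIC is available for every randomised couple.
- The Background argues for an intervention whose effect lasts.

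**The concern.** A group-by-time interaction estimates an intervention effect when one of its occasions precedes treatment. When both occasions follow treatment, it asks only whether the gap between arms widens or narrows after the sessions end. A benefit that is achieved and then held, which is what the investigators hope for, contributes nothing to that contrast. A benefit that fades contributes a lot. A null result could therefore accompany a large lasting gain, and a significant result could reflect loss of benefit.

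The consequences go beyond a single p-value:

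- The section sets a 0.05 significance level for all analyses, and the wording covers HADS and SCORE 15 as well as EPIC.
- The standardised difference observed is to size the definitive trial.
- Phase 1 makes the offer of the intervention to controls depend on a significant quality-of-life benefit, and EPIC is described as part of a quality-of-life measure.
- The Discussion says the study will have established whether the intervention works.

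**Working it through.** **Inputs from the protocol article.** N = 68 couples, 1:1 allocation, so 34 per arm; SD 24 on EPIC sexual function; stated detectable difference 9.6 units; f = 0.20; power 90%; alpha 0.05; two groups, two occasions. **Assumed:** correlation ρ between any two visits. The article gives none, so 0.5 is used, with 0.3 to 0.7 as the range.

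**1. Reproducing the plan's 68.** For the within-between interaction with k = 2 groups and m = 2 occasions, the noncentrality is λ = f²·N·m/(1 − ρ), with (k − 1)(m − 1) and (N − k)(m − 1) degrees of freedom. At ρ = 0.5, λ = 0.04 × 68 × 2 / 0.5 = 10.88 on 1 and 66 df. Power is 0.902, and 68 is the smallest even N reaching 90%. With three occasions at the same ρ, N would be 56. The figure therefore matches a two-occasion interaction.

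**2. What the contrast measures.** Let D_end and D_6m be the arm differences (intervention minus control) at the two visits. Then

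interaction = (M_int,6m − M_int,end) − (M_ctl,6m − M_ctl,end) = D_6m − D_end.

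If D_6m = D_end, this is 0 whatever the size of the benefit, and the rejection rate equals alpha. This is algebra; ρ and the SD play no part.

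**3. Size of the problem.** The standard error of the interaction is 24·√(2(1 − ρ))·√(4/68). At ρ = 0.5 this is 24 × 1 × 0.2425 = 5.82. Simulation (20,000 trials, 34 per arm, SD 24, ρ = 0.5) gave these rejection rates for the test as written:

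| True benefit at end → six months | Rejection rate |
|---|---|
| 9.6 → 9.6 | 5.2% |
| 19.2 → 19.2 | 5.3% |
| 9.6 → 4.8 | 13% |
| 9.6 → 0 | 37% |
| 19.2 → 0 | 90% |
| 0 → 9.6 | 36% |

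The noncentral F agrees. For 9.6 → 0, λ = (9.6/5.82)² = 2.72, power 0.369 (0.279 to 0.555 over the ρ range). For 19.2 → 0, λ = (19.2/5.82)² = 10.88, power 0.902 (0.784 to 0.987).

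**4. Contrasts that use baseline, 9.6 units sustained, 34 per arm.**

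- Change from baseline to one visit: residual SD 24·√(2(1 − ρ)); power 37% (28% to 56%).
- ANCOVA at one visit: residual SD 24·√(1 − ρ²) = 20.8; power 48% (41% to 64%).
- ANCOVA on the mean of both visits: residual SD 24·√((1 + ρ)/2 − ρ²) = 24·√0.5 = 17.0, SE = 17.0·√(2/34) = 4.12, ratio 9.6/4.12 = 2.33, power Φ(2.33 − 1.96) = about 65% (60% to 79%). A separate simulation of 6,000 trials gave 63%.

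For 19.2 units sustained, simulated power for change from baseline is 90% at either visit, and ANCOVA on the mean exceeds 99% at ρ = 0.5. The test as written stays at 5%.

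**5. A consequence for the power statement.** In a 2 × 2 interaction with SD 24, f = 0.20 corresponds to a difference in changes of 4 × 0.20 × 24 = 19.2 units. The stated 9.6 equals 2 × 0.20 × 24. The claim of 90% power for 9.6 units does not follow from the named test, nor does it hold for the contrasts in step 4 at N = 68.

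**The case against.** The best defence is that the parenthesis is a drafting slip. The design is described as pre-test/post-test, three visits are scheduled, and efficacy is defined as a pre/post difference; the authors may have meant a baseline-to-visit comparison at each follow-up. Reproducing 68 does not exclude this, because any two-occasion interaction gives the same number. That is fair as to intent. But the same two post-treatment occasions are written into both the sizing and the analysis sections, and an analyst following the text would run the wrong test.

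A repeated-measures ANOVA also yields a between-arm main effect, which would respond to a sustained difference (about 48% power at 9.6 units, ρ = 0.5). The protocol does not name it as the test or size the trial on it, and it too leaves out baseline.

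The trial is a pilot. Its primary aim is feasibility and acceptability, efficacy is subsidiary, and Data collection says hypotheses are not formally tested. The pre/post mean difference could still be reported correctly alongside an uninformative p-value. This lowers the stakes. It does not remove them, because the article also claims 90% power, sets a significance level, ties the offer to controls to significance and says effectiveness will be determined.

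Two limits stand. The exact 5% applies to a benefit of equal size at both visits; one that grows or partly fades is picked up, but only through its change. All other power figures depend on the assumed correlation.

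**Conclusion.** The concern holds. As written, the only named efficacy test compares the arm difference at six months with that at end of intervention, and it contradicts the pre/post contrast given as the efficacy estimate in the same section. For a benefit of equal size at both visits the chance of rejection is 5%, independent of the benefit, the SD and the correlation. A benefit of 19.2 units that disappears is declared significant in about 90% of trials (78% to 99% for correlations of 0.3 to 0.7). Those last figures rest on 34 completing couples per arm, SD 24 and equal correlation between visits. This should be corrected before analysis, despite the pilot status.

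**What to change.** Replace the sentence in Statistical analysis with a linear mixed model (or ANCOVA) for EPIC sexual function at the two follow-ups, containing arm, visit, arm-by-visit and baseline EPIC as a covariate. Name one primary estimate: the adjusted arm difference with its 95% confidence interval, either at a stated visit or averaged over both. Keep arm-by-visit as a secondary question about durability. Use the same model for HADS and SCORE 15. An interaction with baseline as one of the two occasions would also remove the contradiction, with less precision.

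Correct the matching words in Sample size calculation and redo the power statement for the chosen estimate, stating the assumed correlation. At ρ = 0.5, 90% power for 9.6 units would need 66 per arm completing for the adjusted mean of both visits, or 99 per arm for one visit. For a pilot, it is also reasonable to keep 68 couples and report the expected power or precision honestly.

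The cost is redrafting and a short recalculation, with any separate analysis plan brought into line. No new data are needed, because baseline EPIC is already collected before allocation.
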